## Methods and Design

The current study protocol was approved by the Joint Chinese University of Hong Kong and New Territories East Cluster (CUHK-NTEC) Clinical Research Ethics Committee (CREC).

This study is a randomized controlled trial with three study arms: the MBCT programme led by trained MBCT instructors, Psycho-Education Group (PEG) using CBT principles led by clinical psychologist, and usual care (UC) which will be offered MBCT at the end of the study for ethical reasons. The MBCT and group PEG consist of eight 2-hour weekly sessions. Outcome measures of all participants will be collected at similar time points (baseline, immediately post intervention, and at 3, 6 and 9 months post intervention). The previous studies that evaluated the effectiveness of MBCT for anxiety did not employed a control group; the inclusion of comparison groups, a usual care group and PEG, will be important in evaluating the benefits of MBCT.

Three instructors with at least two-year experience in teaching MBSR or MBCT will lead the MBCT groups while three clinical psychologists with at least master degree in clinical psychology will be hired for conducting the PEG.

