### Data and statistical analysis

Baseline characteristics of the three groups will be compared by ANOVA test for continuous variables and chi-square test for categorical variables. The baseline factors will include age, sex, medication status, psychological and lifestyle characteristics. Our primary end point is the change of anxiety and worry score (BAI and Penn State Worry Scale) from baseline to the end of intervention. Secondary outcomes included the change in scores of CES-D and SF-12. For primary analyses, treatment outcomes will be assessed by ANCOVA, with change in anxiety score as the baseline variable, while the baseline anxiety score and other baseline characteristics that significantly difference between groups will serve as covariates. A two-sided P value of 0.05 or less will be considered be statistically significant. For secondary analyses, the three groups will be simultaneously taken into the analysis of variance model for repeated measures. The baseline measurement of anxiety symptoms and any significant secondary outcome variables will be entered into the model as a covariate as they are considered to be confounders. Analysis will also be performed on an "intention to treat" analysis.

Since there have been no studies on MBCT with an active control that control for contact time and attention, we need to use the only available study on GAD with an active control by Wetherell et al [22] for sample size calculation. The null hypothesis for this study is that there will be no improvement in the outcome measures in the MBCT group relative to other groups and we will test this hypothesis using a one-sided analysis.

Assuming that the average change of mean score of BAI of patients in MBCT is 5.6 (7.4), in the discussion group is 2.0 (7.4) and that in usual care control is 1.1(7.4) with a 1-sided type I error of 5% and 80% power to detect statistical significant differences between the MBCT and psycho-education group as well as MBCT and usual care control, the required sample size is 76 subjects in each group. We set our enrolment target at 228 subjects.

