## Limitations

Participants who volunteer for the study could be biased towards non-pharmacological treatment and those who are assigned to the usual care group may be disappointed and drop out from the study. Although we will offer MBCT at the end of the study, the attrition rate for this group of participants is likely to be higher. Further analysis of the demo-sociographic characteristics of pateints who enrolled in our study will further inform the generalizability of our findings.

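### The 76 patients per group stated as required do not follow from the plan's own inputs, which require 53; the missing step, the sidedness and the proxy status of the active-control figure should be stated

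*Protocol article*

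**What the plan says.** All of the sample size inputs stand in one paragraph of the Protocol article, section Data and statistical analysis. The means and SDs begin "Assuming that the average change of mean score of BAI of patients in MBCT is 5.6 (7.4), in the discussion group is 2.0 (7.4"), and usual care is given a change of 1.1 with the same SD. The error rates are set "with a 1-sided type I error of 5% and 80% power", for two comparisons: MBCT with psycho-education and MBCT with usual care. The result is that "the required sample size is 76 subjects in each group. We set our enrolment target at 228 subjects".

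The paragraph says of the null hypothesis that "we will test this hypothesis using a one-sided analysis". The preceding paragraph of the same section sets a different criterion: "A two-sided P value of 0.05 or less will be considered be statistically significant".

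The section says openly that the figures come from an earlier active-control study in GAD, because no MBCT study had such a control. The active arm of this trial is described under Methods and Design as a "Psycho-Education Group (PEG) using CBT principles led by clinical psychologist". On loss to follow-up, the Limitations section says of the usual care group only that "the attrition rate for this group of participants is likely to be higher". No rate is given anywhere.

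**The concern.** The paragraph makes a complete claim, from inputs to a required number, and the number does not follow from the inputs. Nothing separates the required number from the enrolment target, since 3 x 76 = 228. A reader therefore cannot tell whether 76 is the number to be analysed or the number to be enrolled so that fewer can be analysed.

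That matters in two ways. Monitoring of loss needs to know how many evaluable patients per group keep the trial at its intended power, and 53, 67 to 68 and 76 are all possible readings. The judgement on whether a null result is informative needs the true power, which also depends on whether the test is one-sided or two-sided.

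A separate question is how far the 2.0-point change for a discussion group can stand for a programme based on CBT principles. The comparison with psycho-education is part of the primary objective, and the Discussion names the active control as a key strength.

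**Working it through.** **Inputs** (all from Data and statistical analysis): mean BAI change 5.6 (MBCT), 2.0 (labelled discussion group) and 1.1 (usual care); SD 7.4 in each group; one-sided alpha 0.05; power 0.80; equal groups.

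Differences: 5.6 - 2.0 = 3.6 and 5.6 - 1.1 = 4.5.

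**Attempt to reproduce 76.** Formula: n per group = 2 x (z_alpha + z_power)^2 x SD^2 / difference^2.

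- MBCT versus psycho-education: 2 x (1.645 + 0.842)^2 x 7.4^2 / 3.6^2 = 52.2, so **53**. The t-based calculation gives 52.9, also 53.
- MBCT versus usual care: the same with 4.5^2 in the denominator = 33.4, so **34**.

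The harder comparison governs, so the stated inputs require 53. The stated figure is 76/53 = 1.43 times that.

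**Variants that do not give 76** (difference 3.6):

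| Variant | n per group |
|---|---|
| Two-sided 5%, 80% power | 67 (t-based 68) |
| One-sided 5%, 90% power | 73 |
| Two-sided 2.5%, 80% power | 81 (t-based 82) |
| 80% power for both comparisons jointly, one-sided 5% | 57 |
| 80% power for both comparisons jointly, two-sided 5% | 71 |
| Three-group ANOVA F test, 5%, 80% power | 48 |

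**Variants that reach about 76.** Each needs an input that is unstated or contradicts the text:

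| Variant | n per group |
|---|---|
| 53 with an assumed 30% loss: 53/0.70 = 75.7 | 76 |
| Two-sided 5%, 85% power | 76 |
| One-sided 0.05/3, 80% power | 75 (t-based 76) |
| Two-sided 67 or 68 with an assumed 10% loss | 75 or 76 |
| Design effect with groups of 18 and an assumed intraclass correlation of 0.025: 53 x (1 + 17 x 0.025) = 75.5 | 76 |

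These routes imply different evaluable targets, and the document does not say which, if any, was used.

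**Power on the stated inputs.** Standard error of a difference = 7.4 x sqrt(2/n), which is 1.200 at n = 76 and 1.438 at n = 53. Power = Phi(difference/SE - z), with z = 1.645 one-sided or 1.960 two-sided.

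| Evaluable per group | Comparison | One-sided 5% | Two-sided 5% |
|---|---|---|---|
| 76 | difference 3.6 | Phi(2.999 - 1.645) = 91% | Phi(2.999 - 1.960) = 85% |
| 76 | difference 4.5 | 98% | 96% |
| 53 | difference 3.6 | Phi(2.504 - 1.645) = 80% | Phi(2.504 - 1.960) = 71% |

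**Sensitivity to the active-control assumption, at 76 evaluable.** The difference detectable with 80% power is (1.645 + 0.842) x 1.200 = 2.98 one-sided and (1.960 + 0.842) x 1.200 = 3.36 two-sided. With MBCT held at 5.6, power falls below 80% once psycho-education improves by more than 5.6 - 2.98 = 2.6 points (one-sided) or 5.6 - 3.36 = 2.2 points (two-sided). The document gives no change for a CBT-based arm, so the last two rows below are assumptions:

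| Psycho-education change | Difference | One-sided power | Two-sided power |
|---|---|---|---|
| 2.0 (as stated) | 3.6 | 91% | 85% |
| 3.0 (assumed) | 2.6 | 70% | 58% |
| 4.0 (assumed) | 1.6 | 38% | 26% (t-based; 27% by the normal formula) |

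**The case against.** The strongest defence is that the error is on the safe side. If all 76 per group are evaluable and the inputs are right, the trial exceeds 80% power under either sidedness. A condensed article may simply have dropped a line about loss or multiplicity. This stands, and it lowers the severity. It does not rescue the sentence, which calls 76 the number required for 80% power at one-sided 5%.

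A reader might infer that 76 is 53 inflated for 30% loss. The arithmetic fits, but no such rate is stated, and the attrition remark under Limitations has no figure. Other unstated routes fit about as well. The document does not support choosing one.

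A reader might also infer that the power statement is wrong because the trial has no discussion group. That goes too far. The section says that its figures are borrowed and why, and the section on the Psycho-Education Programme describes an arm meant to match MBCT in structure, therapist contact and attention. A proxy of that kind is legitimate. What stands is narrower: no reason is given why a discussion group's change should apply to a CBT-based programme, when the Background names CBT as a first-line treatment. Against that, the Discussion describes the approach as a low intensity one, and the planned baseline-adjusted ANCOVA may gain precision that these calculations leave out. Whether power is overstated is therefore unknown, and a sensitivity range is the right answer.

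**Conclusion.** The point holds as a should-fix. The stated inputs give 53 per group for MBCT versus psycho-education and 34 for MBCT versus usual care, not 76, and no stated step closes the gap. The mismatch alone does not show an underpowered trial. The 80% claim becomes uncertain only if 76 conceals an allowance for loss: at 53 retained and the two-sided criterion, power is about 71%.

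These figures rest on an unadjusted comparison of two means with a common SD of 7.4, no clustering by therapy group and no correction for two comparisons. The 2.0-point input is a disclosed but unjustified assumption. It is a reason to show sensitivity and does not prove the calculation wrong.

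**What to change.** Restate the sample size paragraph in this order:

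1. Reconcile the one-sided hypothesis and sample size with the two-sided significance criterion, and use one of them throughout.
2. Give the evaluable number per group that follows from the stated inputs: 53 one-sided, or 67 to 68 two-sided.
3. State the adjustment actually used to reach 76, with its value. If there was none, withdraw the claim that 76 is required and give the power it delivers (91% one-sided or 85% two-sided if all are evaluable). A loss rate should not be chosen afterwards because it happens to lead to 76.
4. Keep the source label for the 2.0-point change, and say that it is a proxy from a discussion group in an earlier study and not from a CBT-based arm. Relabelling it as psycho-education would hide this. Add a reason for using it, and give power at 76 for assumed psycho-education changes of 2 to 4 points.

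The cost is wording and a few restated figures. Enrolment stays at 228.

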## Discussion

This will be the first study conducted to investigate the usefulness of MBCT using a control group in the treatment of anxiety symptoms in those with generalized anxiety disorder. One of the key strengths of this proposed study when compared to previous studies in this field is the use of an active control group since most of the previous studies have only employed a pre-post design or lack of an active controls.

Since the active control group is conducted by psychologists using CBT principles, which is the current recommended low intensity intervention by the National Institute of Clinical Excellence (NICE) for patients with GAD who suffer from milder symptoms of anxiety in the UK, the results of this trial will advance current knowledge in the management of GAD and the way that group intervention can be delivered and inform future research. One of the advantages of MBCT is the potential for having larger number of participants when compared to normal CBT group (range from 6-8). In this study, we plan to have larger group size than group size previously adopted by previous investigators of MBCT trial.

If MBCT is shown to be effective in reducing participants' symptoms, further economic analysis can be conducted to further evaluate the cost-effectiveness of this intervention. Moreover, it can be further disseminated in various primary and community settings for helping patients with GAD in the community.

## Limitations

Participants who volunteer for the study could be biased towards non-pharmacological treatment and those who are assigned to the usual care group may be disappointed and drop out from the study. Although we will offer MBCT at the end of the study, the attrition rate for this group of participants is likely to be higher. Further analysis of the demo-sociographic characteristics of pateints who enrolled in our study will further inform the generalizability of our findings.
